### **Intervention:**

Patients randomised to the intervention arm will view the study description document and complete baseline surveys. Following this, they will be automatically delivered the series of 4 clinician-developed videos.

Intervention participants will then either receive a link to the intervention videos once/week via text/email.

Reviewers can view the video series at the following link:

<https://vimeo.com/showcase/7683573>

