#### 1.6 Power and sample size

A sample size of 200 participants (100 per arm) would, allowing for 15% attrition and assuming a standard deviation of 18 as described in other studies, have 90% power (2 sided, type 1 error of 5%) to detect an difference in 90-day AF knowledge of 8.95% between participants in the intervention and control arms of the study, which we consider a significant improvement in knowledge. Previous assessment of the JAFKQ has indicated participant scores 1-month post-test with no educational intervention are unchanged (60.4 [SD = 18.6] vs 62.3 [SD = 18.5];  $p = 0.551$ ). Analysis will follow intention to treat principles with all participants analysed in the arm they have been randomised to. P-values of  $< 0.05$  will be considered significant. Primary outcome analysis will use a two-tailed t-test to assess the difference between mean participant JAFKQ scores (max score = 100%). Analysis will also be performed utilizing an Analysis of Covariance (ANCOVA), with baseline JAFKQ scores and education level incorporated into the model as covariates.

For secondary analysis of satisfaction with clinical care, patient responses will be dichotomised into ‘highly satisfied’ ( $\geq 6/7$ ) vs ‘not highly satisfied’ ( $\leq 5/7$ ). For medication adherence, patients will be classified as “adherent” or “not adherent”. Proportions in intervention vs control arms will be compared using a chi-squared test. Relative risk will be calculated using a log binomial unadjusted and adjusted for total time in clinic (for outpatients) and number of medications. Allowing for 15% attrition and assuming 60% satisfaction/medium or greater adherence in the control groups, a sample size of 200 (100 per arm) would have 90% power to detect a relative risk difference in satisfaction and adherence between control and intervention groups of 1.37 (that is, an increase from 60.0% to 82.2%).

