## 3. Analysis

### 3.1 Analysis Principles

#### General methodology

All statistical tests will be two-tailed, and a 5% significance level adopted throughout.

Analyses will be performed according to the principal of intention to treat and will include all randomised patients.

Summaries of continuous baseline variables will be presented as means and standard deviations together with medians and inter-quartile ranges. Categorical variables will be presented as frequencies and percentages. All

continuous data will be checked for normality

Methods for handling missing data are described in 3.2 – sensitivity analysis. If 80% of survey data is available, missing data will be imputed. Participants with less than 80% of outcome data available for a given survey will be removed from analysis.

Baseline values of the analysed parameter will be used as a covariate for analysis that support covariates, if these are not available see approach described below.

Balance in baseline risk factors will be considered between intervention and control groups, and if significant differences exist, additional regression analysis of outcome variables adjusting for this difference will be performed.

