### 3.3 As Treated Analyses

We will also perform an as treated analysis examining all primary and secondary outcome variables with respect to their engagement with the study intervention. Highly engaged participants will be those that watched study videos on 3 or more occasions, moderately engaged participants those who watched study videos on 1-2 occasions and poorly engaged participants those who did not watch study videos.

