#### 5.1.2 As treated analysis of primary and secondary outcomes:

An as treated analysis of all primary and secondary outcomes will also be performed to assess the impact of intervention engagement on study outcomes.

Highly engaged participants will be defined as those watching the video series 3 or more times throughout the intervention period. Moderately engaged participants those watching the series 1-2 times, and poorly engaged participants those who did not watch the video series. Each intervention group will be compared to the control group in the same analyses described above (tables 10-12).

*eTable 10: Sub-group analysis of poorly engaged intervention participants*

|  | Control | Poorly | RR [95% CI] | RR [95% CI] | p-value |
|--|---------|--------|-------------|-------------|---------|
|--|---------|--------|-------------|-------------|---------|

|                                                                    | N C (%)                  | engaged
Intervention
N T (%) | (Control vs
CPR video)
[unadjusted] | (Control vs
CPR video)      | [adjusted] |
|--------------------------------------------------------------------|-------------------------------------|-----------------------------------------------|-------------------------------------------|--------------------------------|------------|
| Jessa Atrial Fibrillation Knowledge Questionnaire score (%) |                                     |                                               |                                           |                                |            |
| Mean score 2
days post
intervention                          | (n=xx)
Mean (SD)
Median (IQR) | (n=xx)
Mean (SD)
Median (IQR)           |                                           | Mean
Difference
(95% CI) | p-value    |
| Mean score 90
days post
intervention                         | (n=xx)
Mean (SD)
Median (IQR) | (n=xx)
Mean (SD)
Median (IQR)           |                                           | Mean
Difference
(95% CI) | p-value    |
| Satisfaction                                                |                                     |                                               |                                           |                                |            |

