| Jessa Atrial Fibrillation Knowledge Questionnaire score (%) |                                      |                                                             |                                               |                |
| Mean score 2 days post
intervention                             | (n=xx)
Mean (SD)
Median (IQR)  | (n=xx)
Mean (SD)
Median (IQR)                         | Mean Difference (95% CI)                      | p-value        |
| Mean score 90 days post
intervention                            | (n=xx)
Mean (SD)
Median (IQR)  | (n=xx)
Mean (SD)
Median (IQR)                         | Mean Difference (95% CI)                      | p-value        |
| Satisfaction                                                |                                      |                                                             |                                               |                |
| Highly satisfied*                                                  | (n=xx)
Proportion (%)             | (n=xx)
Proportion (%)                                    | RR (95% CI)                                   | p-value        |
| Motivation to maintain medication adherence                 |                                      |                                                             |                                               |                |
| Highly motivated* 2
days post intervention                      | (n=xx)
Proportion (%)             | (n=xx)
Proportion (%)                                    | RR (95% CI)                                   | p-value        |
| Highly motivated* 90
days post intervention                     | (n=xx)
Proportion (%)             | (n=xx)
Proportion (%)                                    | RR (95% CI)                                   | p-value        |
| Medication adherence                                        |                                      |                                                             |                                               |                |
| Adherent** to
medications 90 days post
intervention          | (n=xx)
Proportion (%)             | (n=xx)
Proportion (%)                                    | RR (95% CI)                                   | p-value        |

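### The engagement tables (SAP eTables 10-12) group 2-day outcomes by viewing that can come later and test self-selected viewers against all controls, so they can show a dose gradient with no true effect

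*Combined protocol and SAP*

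**What the plan says.** SAP 5.1.2 defines the top engagement level thus: "Highly engaged participants will be defined as those watching the video series 3 or more times throughout the intervention period". One or two viewings of the series is moderate and none is poor. It continues: "Each intervention group will be compared to the control group in the same analyses described above". The stated aim is causal: to gauge what engagement does to the outcomes.

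eTables 10-12 carry six rows each, with p-values: JAFKQ at 2 and 90 days (the former labelled "Mean score 2 days post" intervention), satisfaction, motivation at 2 and 90 days, and adherence at 90 days. By the data collection schedule (SAP 1.7), satisfaction is collected only post-clinic or within 2 days of delivery.

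SAP 3.3 describes the same analysis with another count: "Highly engaged participants will be those that watched study videos on 3 or more occasions".

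Under Protocol section 4 (Intervention), the four videos are delivered straight after the baseline surveys, and participants then "receive a link to the intervention videos once/week via text/email". No end date for the links is given, and the intervention period is not defined. SAP 3.5.1 accepts a 2-day survey as on time up to day 7.

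The analyses carried over are those of SAP 4.1.1 and 5.1.1: ANCOVA or log-binomial models adjusted for age, gender, education and AF subtype, plus unadjusted t- and chi-squared tests. SAP 3.1 adds the baseline value where one exists; SAP 4.1.1 does not list it. On significance, SAP 3.1 says: "All statistical tests will be two-tailed, and a 5% significance level adopted throughout".

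**The concern.** There are two separate problems.

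- **Time order.** For the three early rows, group membership depends partly on behaviour after the outcome was recorded. Later viewing cannot have caused a 2-day score, but a well-informed, motivated or satisfied patient may be more likely to keep watching. Covariates measured at baseline do not repair this.
- **Selection.** For the 90-day rows, patients who chose to watch three or more times are compared with controls who made no such choice. The comparison is no longer randomised. If keen viewers would have scored higher anyway, the high group looks better than control and the non-viewers look worse.

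At stake is a poor-to-high gradient with p-values that could be reported as a dose-response when it shows only who watches. The SAP gives no warning about self-selection, no landmark rule, and no method that keeps the randomised comparison.

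**Working it through.** **1. Timing.** First delivery is at day 0, and weekly links follow at about days 7 and 14. The third prompted viewing therefore falls around day 14, after the 2-day survey and beyond its 7-day window. Unprompted repeats could come sooner, but the plan does not restrict the count to them. This step needs no assumption about the size of any bias.

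**2. The plan's own yardstick.** SAP 1.6 claims to "have 90% power (2 sided, type 1 error of 5%) to detect an difference in 90-day AF knowledge of 8.95" points, "assuming a standard deviation of 18 as described in other studies". With 100 per arm and 15% attrition, 85 per arm remain: 18 × √(2/85) × (1.960 + 1.282) = 8.95. This reproduces. The documents give no figure for the engagement tables, so 8.95 serves only as a scale.

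**3. Unadjusted comparison, true effect zero.** Assumptions not in the documents: the top 28 of 85 are highly engaged, and propensity to view has correlation r with 90-day JAFKQ.

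- Fraction f = 28/85 = 0.329; normal cut-point z = 0.44; density φ(z) = 0.362; mean shift φ(z)/f = 1.099 SD.
- Expected difference from control = r × 1.099 × 18 = 19.8r.
- Standard error = 18 × √(1/28 + 1/85) = 3.92. The rejection rate comes from the noncentral t on 111 df.

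| r | Spurious difference | Difference/SE | Test positive at 5% |
|---|---|---|---|
| 0.1 | 2.0 | 0.50 | 8% |
| 0.2 | 4.0 | 1.01 | 17% |
| 0.3 | 5.9 | 1.51 | 32% |

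For scale, 5.9/8.95 = 0.66.

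**4. With the baseline score in the model.** Further assumption: baseline-outcome correlation 0.6, so the outcome is 0.6 × baseline + 0.8 × residual in SD units. Let viewing correlate ρb with baseline and ρp with the residual, so that r = 0.6ρb + 0.8ρp. ANCOVA removes the baseline part. What remains is 0.8ρp × 1.099 × 18 = 15.8ρp, with standard error about 0.8 × 3.92 = 3.14. Four ways of reaching r = 0.3:

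| ρb | ρp | Adjusted difference | Test positive |
|---|---|---|---|
| 0.50 | 0 | 0 | 5% |
| 0.30 | 0.15 | 2.4 | about 12% |
| 0.17 | 0.25 | 3.95 | 23-24% |
| 0 | 0.375 | 5.9 | 47% |

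Adjustment removes the bias if selection runs only through baseline and shrinks it if partly so. It does nothing for the bias if selection is unrelated to baseline; the smaller standard error then makes a false positive more likely.

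**5. Shape of the gradient.** A null simulation (85 per arm, equal thirds, 4,000 replicates, same 0.6 correlation) at r = 0.28 gave +5.5 / +0.1 / -5.4 points for high / moderate / poor versus control unadjusted, and +3.1 / 0.0 / -3.1 after ANCOVA. With viewing unrelated to outcome it gave 0.1 / 0.1 / 0.1 and about 5% false positives.

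**6. Share highly engaged.** At r = 0.3 unadjusted, a share of 11% gives 9.3 points and 31%, and a share of 50% gives 4.4 points and 25%.

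**7. Definitions side by side.** SAP 3.3 counts occasions of watching any study video; SAP 5.1.2 counts viewings of the series. A patient who watches one video on three days is highly engaged under 3.3 but not under 5.1.2.

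**The case against.** The strongest reply is that none of this need produce a gradient. The documents give neither the size nor the sign of the viewing-outcome correlation. Patients with poorer knowledge might rewatch more, which would reverse the pattern. JAFKQ is collected at baseline, and adjusted models are among those carried over, so unadjusted figures alone would misdescribe the plan. The analysis is additional, and intention to treat governs the primary conclusion. The first viewing is also delivered before the 2-day survey, so part of the classification does precede that outcome.

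Much of this stands. A reader might infer that the tables are bound to show a dose effect even if the videos do nothing; the documents support only that they can. A reader might also infer that viewing is counted over the full 90 days, but the period is undefined. Nor do 5.9 points and 32% describe the adjusted analysis.

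The reply does not remove the point. The unadjusted test is also planned, SAP 4.1.1 leaves baseline JAFKQ out of its covariates, and eTables 11-12 have one effect column not marked adjusted or unadjusted. Satisfaction has no baseline value to adjust for. Some viewing before the 2-day survey does not help when the levels are separated by the total count.

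**Conclusion.** The point holds in two parts of different strength. The time-order fault in the 2-day JAFKQ, 2-day motivation and satisfaction rows follows from the text alone, provided that the intervention period runs past the early survey, as weekly links imply. The selection fault in the 90-day rows is structural, but its size is conditional. With zero true effect, a third of the arm highly engaged and correlations of 0.1 to 0.3, the unadjusted test shows 2.0 to 5.9 points with 8% to 32% false positives. At 0.3, baseline adjustment leaves roughly 2.4 to 3.9 points and 12% to 23% when selection runs partly through baseline, and nothing when it runs only through baseline. The correlations, the one-third share and the 0.6 baseline-outcome correlation are assumptions; the SD of 18 and 85 per arm come from the plan.

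The two engagement definitions conflict, and the documents give no basis for preferring either. It would go too far to conclude that the trial's primary result is compromised: the randomised comparison is untouched.

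**What to change.** - In eTables 10-12, drop the 2-day JAFKQ, satisfaction and 2-day motivation rows, or classify participants for those rows only by viewing completed before that survey.
- Show the 90-day engagement groups descriptively (means or proportions, no p-values), labelled exploratory and non-causal.
- Reconcile SAP 3.3 with 5.1.2 in one definition of engagement, and state the period over which viewing is counted.
- Optional, if an effect of viewing is wanted: add a complier-average effect with randomised arm as instrument. Controls are sent the links only after 90-day follow-up (Protocol 10.5), which suits this design. It answers a different question from viewing levels, so the SAP must state the exposure (any viewing or whole series), the exclusion assumption and the effect measure for binary outcomes. With a whole-series exposure, the exclusion assumption fails if partial viewing helps; the weekly messages might also act on adherence directly.

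The cost is SAP wording and fewer p-values to report, plus one more model with a wider confidence interval if the optional analysis is added.
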